[figure not shown]

**Study Synopsis**

Study Code Number: RESCUE COPD 001

REC Number 15/SC/0216

UKCRN Number PHT/2015/39

Title of the Trial A randomised controlled feasibility trial of E-health platform Supported Care vs Usual care after Exacerbation of COPD

Development Phase: Exploratory Clinical

Principle Investigator: [name]

Sponsor: Portsmouth Hospitals NHS FT

Purpose of Clinical Trial To assess the feasibility of undertaking a randomised controlled trial to determine the effectiveness of E-health platform Supported Care in improving patients outcomes after exacerbation of COPD

Objectives Usability of platform  
Symptom Control  
Inhaler technique  
Treatment adherence  
Quality of Life

Trial Design: A two parallel arms non-blinded randomised controlled feasibility trial

Planned Trial Period: Participant follow up: 90 days approximately  
Recruitment Period 6 months

Intervention (description, frequency, details of delivery) The study will deliver two interventions one to each arm of the study. One group will be randomised to myCOPD an online self management system and the other group to a conventional written self management plan. Details of the interventions can be found on pages 14 and 15 and Appendix 3 of this protocol.

Outcomes: Trial feasibility outcomes:

- Recruitment rate
- Withdrawal and loss to follow-up rate
- Usability of the of E-health platform

- Use of the of E-health platform
- Completeness of data collection

#### Intervention effectiveness outcomes

- COPD Assessment Tool (CAT) Score
- Improvement in number of critical errors for Inhaler Technique
- Quality of Life score: St Georges Respiratory Questionnaire (SGRQ)
- modified Medical Research Council Dyspnoea Questionnaire (mMRC)
- Patient Activation Measure (PAMs)
- Hospital Anxiety and Depression Score (HADS)
- COPD treatment adherence
- Safety

Sample size 60

Study Population:

- Adult, male and female COPD patients following admission to hospital or supported care with exacerbation
- Age Range 45-80 years

Study Procedures

- Informed Consent
- Clinical History and Physical Examination
- Inhaler Technique Assessment
- PROMs
- CAT
- SGRQ
- mMRC
- HAD
- PAM
- VSAQ
- WPAI
- SMP training
- Safety- AE & SAE capture
- Qualitative interview

Inclusion Criteria:

1. Subjects able to complete all study procedures and give written informed consent.
2. A diagnosis of COPD defined as per the NICE COPD guidelines
3. Male or female volunteers aged 45+ admitted to hospital or the ambulatory care service with a primary diagnosis of acute exacerbation of COPD
4. Patients who are taking inhaled therapies

for COPD

5. Current or ex-smokers with a pack year history of more than 10 years
6. Access to the internet and ability to operate web platform and or use written action plan

- Exclusion Criteria:
1. Patients who have any another respiratory disease as their main complaint such as asthma, bronchiectasis, lung cancer, tuberculosis or any other significant respiratory disease.
  2. Patients unable to read or use an Internet enabled device.
  3. Patients with any uncontrolled medical condition which in the view of the principle investigator or their team would confound the impact of a COPD directed support tool.
  4. Sensitivity or allergy to saccharin

Study Schedule Outline: Day 1: A detailed study schedule appears in **Appendix 1.**

Follow Up Duration: 90 days (+/- 7 days) after hospital discharge for COPD exacerbation

Statistical Methods: Demography: descriptive statistics will be provided.  
Adverse events: will be described descriptively.  
ITT analysis of change of CAT score between treatment groups  
ITT Analysis of incidence of critical errors in inhaler technique at d90  
Comparative analysis of secondary and exploratory outcomes between study arms

**List of Abbreviations**

|            |                                                     |
|------------|-----------------------------------------------------|
| E – Health | Electronic Health                                   |
| mHealth    | Mobile Health                                       |
| AE         | Adverse Event                                       |
| CAT        | COPD Assessment Tool                                |
| COPD       | Chronic Obstructive Pulmonary Disease               |
| CRF        | Case Report Form                                    |
| CTM        | Clinical Trial Material                             |
| EC         | Ethics Committee                                    |
| GCP        | Good Clinical Practice                              |
| HAD        | Hospital Anxiety and Depression score               |
| ICH        | International Conference on Harmonization           |
| ID         | Identification                                      |
| IEC        | Independent Ethics Committee                        |
| ITT        | Intent To Treat                                     |
| mMRC       | Modified Medical Research Council Dyspnoea score    |
| PAM        | Patient Activity Measurement                        |
| PIC        | Participant Identification Centre                   |
| PROMS      | Patient Recorded Outcome Measurements               |
| SAE        | Serious Adverse Event                               |
| SAP        | Statistical Analysis Plan                           |
| SGRQ       | St Georges Respiratory Questionnaire                |
| SMP        | Self Management Plan                                |
| VSAQ       | Veterans Specific Activity Questionnaire            |
| WPAI       | Work Productivity Activity Impairment Questionnaire |

## **Introduction and Background**

### **Aims and Objectives**

The primary aim of this study is to investigate feasibility of undertaking a trial to determine the impact on patient outcomes of an interactive web-based patient self-management and action plan in comparison to a written action plan in current use. The usability of the platform and its effect on symptom control, inhaler technique, treatment adherence and quality of life will be studied in subjects recruited from patients recently admitted to hospital or to specialist ambulatory care for the treatment of an exacerbation of COPD, using validated tools and questionnaires. The safety and efficacy of the novel intervention will be reported and findings will contribute to the design and implementation of larger future studies.

### **Background and Significance**

COPD is characterised by airflow obstruction that is not fully reversible. The airflow obstruction is usually progressive in the long term and results in the gradual development of limiting symptoms such as cough and breathlessness. Cigarette smoking is the predominant cause of COPD, but other factors, particularly occupational exposures, may also contribute to the development of COPD. Exacerbations occur when there is a rapid and sustained worsening of symptoms beyond normal day-to-day variations, these are often associated with acute respiratory infections and can result in unscheduled health care use and hospitalisation.

There are currently 900,000 patients diagnosed with COPD in the UK. COPD is the second leading cause for hospital admission in the UK; recent figures show that one in three people with COPD is readmitted within 28 days of discharge. The latest Quality Standards for COPD from the National Institute for Health and Care Excellence (NICE) highlights the importance of self-management for patients and recommends that every person diagnosed with COPD be given an individualised comprehensive self-management plan. Self-management has been shown to be associated with health service utilisation by COPD patients, improve their quality of life and reduce hospitalisation.

Patients with COPD are often prescribed a complex combination of inhaled medications in a variety of devices; these medications differ enormously in their delivery method and periodicity. This complexity contributes to poor compliance and therefore wasteful prescribing and it is estimated that there is currently only at best a 30% compliance to COPD medications.

The majority of COPD action plans are delivered in a written (paper) format, and currently a validated online interactive solution does not exist. *MyCOPD* has been designed and programmed by my mhealth Ltd with patient and clinician involvement. It is a web-based self-management system designed to encompass the principles of supporting self-care in people with COPD. The system can be easily and securely accessed online by patients and healthcare

professionals to facilitate the effective recognition of symptoms, inhaler technique and management of medicine for patients with COPD. In 2013 myCOPD was tested in a COPD population as part of a service development project. 36 people with COPD tested myCOPD and the results of the study showed 95% demonstrated a decrease in symptom score and an overall improvement in inhaler technique. There are numerous written self management plans available which have been developed and produced by individual Trusts, GP surgeries and pharmaceutical companies. The written Self management plan we intend to use for comparison was developed by HealthQuest Solutions Ltd in partnership with Novartis, as part of a national programme. This self management plan to date has been delivered to over 50,000 patients across the UK.

An initial design and optimisation phase of MyCOPD development demonstrated that the tool is usable in this patient group. Patients testing the platform demonstrated regular and effective daily use with associated improvements in inhaler technique and symptom control. Patients fed back that the platform was easy to use, reliable and that it would become part of their daily treatment regime if available.

### **Purpose of trial**

In a group of patients with COPD, discharged from hospital with an acute exacerbation at their 2 week review we will undertake a feasibility trial to test the design and obtain preliminary evidence that the MyCOPD web based self-management plan will result in greater improvements in quality of life scores, faster recovery to baseline, and fewer errors in inhaler technique compared to conventional paper based plans. The result from this trial will inform the design and sample size calculation for a definitive trial to determine the effectiveness MyCOPD

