**Intervention effectiveness outcomes**

- The time to a two-point improvement in the COPD Assessment Tool (CAT) Score
- The improvement in CAT score at study completion 90(+/- 7) days in the MyCOPD support population compared to usual care
- The number of critical errors by inhaler at study completion 90(+/- 7)
- St Georges Respiratory Questionnaire (SGRQ) score at study completion 90(+/- 7)
- Modified MRC dyspnoea score at study completion 90(+/- 7)
- Patient Activation Measure (PAMs) score at study completion 90(+/- 7)
- Hospital Anxiety and Depression Score (HADS) at study completion 90(+/- 7)
- WPAI score at study completion 90 (+/- 7)
- VSAQ score at study completion 90 (+/- 7)
- COPD treatment adherence (what would be monitored and how would this be measured?)
- The number of exacerbations by study completion 90(+/- 7) days
- The time to exacerbations
- The rate of and timing of antibiotic use by study completion 90(+/- 7) days
- The rate of and timing of steroid use by study completion 90(+/- 7) days
- Safety the number of AEs and SAEs by study completion 90(+/- 7) days

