### **Visit 1- Consent and Screening**

Patients wishing to participate as above, will within 2 weeks of hospital discharge (+/- 1 week) at Visit 1 initially give written informed consent. This visit may occur at the hospital, in primary care or at the patient's home depending on patient preference.

Clinical data will be captured. Symptom scores will be calculated using the COPD Assessment Tool (CAT), SGRQ, modified Medical Research Council Dyspnoea Questionnaire (mMRC) Patient Activation Measure (PAM), Work Productivity Activity Impairment (WPAI) and the Veterans Specific Activity Questionnaire (VSAQ). At this visit the team will also record the admission and exacerbation history, video the inhaler technique and complete an inhaler critical errors assessment.

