### **COPD Assessment Tool (CAT) Questionnaire**

This is a validated symptom scoring system used in COPD studies The CAT questionnaire contains eight questions and provides a reliable measure of the impact of COPD on health status. Patients read the two statements for each item, which describe the best and worst scenario, (e.g I never cough – I cough all the time), and decide where on the scale of 0-5 they fit. The maximum score is out of 40. The higher the CAT score the greater the impact of symptoms on their health status. Experts involved in the development of CAT suggest that any change of 2 or more in the patient's final score may indicate a clinically significant change.

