### **Statistical Methods**

The analysis of the trial feasibility aims will be primarily descriptive. Summary statistics will be calculated to assess aims such as the recruitment and retention rate, frequency of access and use over time of the E-health platform. A list of key study variables will be drawn up and the proportion missing by time point and arm will be calculated.

All intervention effectiveness outcome measures will be summarised by intervention arm using means and standard deviations or median (range, IQR) for continuous outcomes (as appropriate), and frequencies and proportions for categorical outcomes. As this is a feasibility study with only 30 participants per arm the trial will be underpowered to detect statistically significant differences in outcome measures between arms, however the difference between arms will be estimated and presented with 95% confidence intervals to indicate the uncertainty of the estimate. The estimation analyses will be undertaken using an intention-to-treat approach i.e. participants will be analysed in the arm to which they were randomised regardless of whether or not they subsequently used self-help online or via usual care approach or their adherence to the intervention.

The time to a two point increase in CAT score will be plotted using the method of Kaplan-Meier and Cox proportional hazards model will be used to estimate the relative 'risk' between arms by means of a hazard ratio. An analysis of covariance model will be used to obtain an estimate for the mean difference in CAT score at final study visit (90 days) between the two intervention arms adjusted for baseline CAT score. In addition CAT values over time will be plotted for individual and the mean value over time displayed by intervention arm. A longitudinal analysis will then be undertaken using a linear mixed model including baseline CAT as a covariate with random subject effects using (if possible) a structured (symmetrical) covariance matrix. Model assumptions will be assessed through residual analysis.

Every effort will be made to obtain 90- day follow up data for all participants including those that have withdrawn from the trial by offering a home visit if required to obtain this information.

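### Recovery to baseline is a stated purpose, but no usual-state symptom level is collected in both arms and the two-point CAT outcome does not measure a return to one

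*Protocol*

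**What the plan says.** The Purpose of trial section describes patients discharged after an acute exacerbation and seen at their 2-week review. The trial is to "obtain preliminary evidence that the MyCOPD web based self-management plan will result in greater improvements in quality of life scores", and also "faster recovery to baseline, and fewer errors in inhaler technique compared to conventional paper based plans".

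Among the intervention effectiveness outcomes, the only one that times recovery is "The time to a two-point improvement in the COPD Assessment Tool (CAT) Score". The outcome list names no reference score and no confirmation rule. The CAT section explains where the two points come from: the developers of the tool "suggest that any change of 2 or more in the" final score may be clinically significant. It also fixes the direction: "The higher the CAT score the greater the impact of symptoms on their health status".

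The first CAT is taken when patients "will within 2 weeks of hospital discharge (+/- 1 week) at Visit 1" give consent. Appendix 1 shows only the information sheet on Day 1, then CAT at Visit 1, days 30 and 60, and the 90-day visit.

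The Statistical Methods section names the event in the opposite direction: "The time to a two point increase in CAT score will be plotted using the method of Kaplan-Meier".

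**The concern.** Baseline in the purpose statement can only sensibly mean the patient's usual state before the exacerbation. If it meant the Visit 1 score, every patient would already be there and recovering to it would have no content. To say whether one arm recovers faster, the trial needs that usual level, or at least a question about whether the patient is back to it, in both arms. Neither is planned. A statistical analysis plan cannot supply a reference level that was never collected.

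The two-point outcome does not fill the gap. It records a change of a given size, whatever the distance from usual. A patient already back to normal at Visit 1 has nothing left to recover, and a patient far above normal meets the event after a small fall.

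Two things are at stake. The report could describe a two-point fall as recovery to baseline, which the data would not support. And since the trial is meant to help choose the definitive trial's primary outcome, this candidate should be judged for what it measures. The reversed direction in Statistical Methods adds to this: as written, the analysis section estimates no time to improvement at all.

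**Working it through.** **1. Is a usual-state level collected anywhere?** Going through the Protocol's data sources:

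- Day 1 case identification: information sheet only (Appendix 1).
- Visit 1: CAT and the other questionnaires, first taken here, after the exacerbation.
- Clinical Data and PROMs: history, treatments, lung function and co-morbidities from notes. No symptom score is named.
- Exacerbation History and Admission History: the count of exacerbations in the prior year, and admissions. These are not symptom levels.
- SGRQ Part 1: 3-month recall, a period that includes the exacerbation.
- The app's daily status, which includes a normal-for-me option: myCOPD arm only, and not a listed outcome.

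No source gives a pre-exacerbation symptom level in both arms.

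**2. The Protocol's own precision figure.** Inputs from Sample size rationale: CAT SD 6.5, 30 per arm. Half-width of the 95% interval for the difference = 1.96 × 6.5 × √(2/30) = 3.29, which reproduces the stated ±3.3. The Protocol gives no figure for the time-to-event outcome.

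**3. What a two-point fall means relative to usual.** Let G be the number of points by which a patient's Visit 1 CAT exceeds usual. G is not in the documents; take 2, 5 and 8 as illustrations. After a fall of exactly 2, the patient is still G − 2 points short:

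| G | Points above usual when the event is met |
|---|---|
| 2 | 0 |
| 5 | 3 |
| 8 | 6 |

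The same event is full recovery for one patient and partial recovery for another, and without G they cannot be told apart.

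**4. How often the event occurs with no true change.** Assume test-retest reliability r of 0.7 to 0.9 (not in the documents). Error SD of one reading = 6.5 × √(1 − r). SD of the difference of two readings = 6.5 × √(2(1 − r)). With whole-point scores, a fall of at least 2 at day 30 has probability close to Φ(−1.5 / SD of difference). For any of the three later readings, which share one Visit 1 score, the figure comes from a simulation of 400,000 patients.

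| r | Error SD | SD of difference | Fall ≥2 at day 30 | Fall ≥2 at any of days 30, 60, 90 |
|---|---|---|---|---|
| 0.7 | 3.56 | 5.03 | 38% | 63% |
| 0.8 | 2.91 | 4.11 | 36% | 60% |
| 0.9 | 2.06 | 2.91 | 30% | 53% |

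The last column assumes that any single reading counts, which the Protocol does not state. If the fall had to be present at two consecutive readings, the no-change rate would be 22% to 29%.

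**5. Direction.** Improvement in the outcome list is a fall, because a higher CAT is worse. An increase in Statistical Methods is therefore deterioration. The two sections define opposite events.

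**The case against.** The strongest reply is that this is one phrase in a purpose paragraph of a feasibility trial. It asks only for preliminary evidence. Recovery to baseline is not among the specific objectives or the listed outcomes, and no primary outcome is set. That stands: no listed endpoint becomes unanswerable, and the defect is mainly one of wording.

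Second, Statistical Methods also plans individual and mean CAT plots over time, a longitudinal mixed model adjusted for baseline CAT, and an analysis of covariance at 90 days. These describe the course of symptoms by arm without any threshold, and noise common to two randomised arms dilutes a contrast rather than creating one. That also stands. But these analyses show change from Visit 1, not return to usual.

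Third, whether a fall must be confirmed is ordinary content for a statistical analysis plan. I agree, so the absence of a confirmation rule is not part of this point.

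Fourth, a recalled CAT is not a clean remedy, because the form asks about the patient's current state. Suppose recall error equals ordinary CAT error, r is 0.7 to 0.9, and recovery means no more than 2 points above the recalled level, held at the next contact or present at the last visit. In simulation that rule calls 23% to 37% of patients who remain 5 points above usual recovered, and misses 12% to 22% of those back to usual throughout. This is why such a measure should be exploratory only.

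A reader might also infer that almost everyone will meet the event, because in the pilot "95% demonstrated a decrease in symptom score". The documents do not support that. The score is unnamed, the size and timing of the decrease are not given, all 36 people used the app, and they are not described as post-exacerbation patients. Nor does the Protocol say how far patients have recovered by Visit 1, so it cannot be asserted that the first CAT falls part-way through recovery.

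**Conclusion.** The point holds in limited form. Faster recovery to baseline, as written, cannot be answered, because no usual-state symptom level is collected in both arms and the one recovery-type timing outcome measures a clinically relevant change. Statistical Methods then names the opposite event. This follows from the text alone and needs no assumption beyond reading baseline as the patient's usual state.

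The size figure is illustrative. The 53% to 63% rests on the Protocol's SD of 6.5, an assumed reliability of 0.7 to 0.9, normally distributed error, no true change after Visit 1, and any single reading counting. It shows that the event cannot be read as recovery. It does not show that the outcome is useless for comparing arms, or that the trial fails in its feasibility aims. Severity is minor to moderate.

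**What to change.** Two wording changes are enough:

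- In Purpose of trial, replace the phrase on recovery to baseline with time to a fall of at least two CAT points from the Visit 1 score.
- In Statistical Methods, change the two-point increase to a two-point improvement (decrease), and make the same change where the time-to-exacerbation analysis refers back to it, so that the section matches the outcome list.

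These cost nothing beyond the edit, and no recovery claim is then made. A rule requiring the improvement to be sustained can be added as a sensitivity analysis.

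If recovery to usual is to remain a purpose, collect a usual-state reference in both arms at Visit 1, before the randomisation that closes that visit. A recalled usual-state CAT is one option. Report return to that level as exploratory only. The cost is one extra 8-item form at a visit already held. The downside is recall error and the misclassification described above, but allocation cannot influence a reference taken before randomisation.
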